### Adherence and Fidelity Procedure

Adherence and fidelity are monitored through multiple methods to maintain consistent delivery and meaningful engagement in each session. CHWs complete a structured adherence checklist after every session, documenting session completion, participant attendance, in-session worksheet, and lesson review completion. At the conclusion of each session, the youth-caregiver dyad is asked to complete a post-session survey designed to assess session quality, coaching effectiveness, and perceived impact. This survey includes Likert-scale items that explore how helpful the session was and how well the CHW facilitated discussion. These responses help monitor the fidelity of the coaching relationship and the content delivery.

Periodic observations by the project coordinator further support quality assurance, allowing for feedback for CHWs. A minimum of 10 percent of CHW’s recorded coaching sessions are watched and reviewed by the program coordinator to ensure fidelity. The coordinator meets regularly with CHWs to discuss progress with dyads, room for improvement, and ways to resolve any arising conflict between youth and caregiver. The project coordinator and CHWs also collaborate to ensure dyad retention within the program if notable barriers to attending sessions are observed. In addition, trial oversight is maintained by the data management team that includes the principal investigator, project coordinator, and co-investigator (i.e., statistician) through weekly review of enrollment progress and protocol adherence in accordance with IRB requirements.

### Intervention Group: Garnering Resilience in Traumatized Youth and Families

Participants randomized to the intervention group will receive GRIT, a six-session psychoeducational health coaching intervention designed to promote self-regulation and healthy habit development. GRIT is delivered to adolescent–caregiver dyads using a trauma-informed, coaching-based approach that emphasizes responsive communication and skill practice. Adolescents and caregivers may attend sessions jointly or individually, as needed.

To support skill acquisition and ongoing practice, each dyad is provided with an Inner Balance Trainer made by HeartMath^®^ and instructed in heart rate variability biofeedback (HRV-BF) practice. CHWs introduce and reinforce HRV-BF throughout the intervention, and regular practice using HRV-BF is incentivized through monthly competitions based on the total number of minutes practiced. Participants retain the device following the study’s completion to support continued use.

#### Content.

GRIT integrates components from Trauma-Focused Cognitive Behavioral Therapy (TF-CBT), Acceptance and Commitment Therapy (ACT), and the Shift and Persist framework. The curriculum emphasizes psychoeducation and skills to enhance self- and co-regulation, stress management, communication, and resilience. Core content includes education on toxic stress and Adverse Childhood Experiences (ACEs), emotion identification, diaphragmatic breathing, heart rate variability biofeedback (HRV-BF), cognitive reframing, values clarification, and goal setting. Later sessions focus on the California Surgeon General’s recommendations for preventing toxic stress through healthy habit formation (e.g., nutrition, sleep, and positive relationships) and communication strategies that support responsive caregiving and family functioning.

This intervention is delivered by community health workers (CHWs) who completed a trauma-sensitive HeartMath^®^ certification course called Resilient Heart^™^ and training on the GRIT intervention protocol prior to participant enrollment. The GRIT training includes a minimum of 10 weeks of training on foundational GRIT concepts, including 10 self-study modules delivered as an online course. Each CHW is also required to develop their own self-care practice, which includes applying concepts of Cognitive Behavioral Therapy (CBT) and Acceptance and Commitment Therapy (ACT) to their own lives as well as practicing self-regulation techniques using HeartMath’s Inner Balance Trainer. Each CHW completes practice sessions to demonstrate their coaching skills and receive structured feedback. The CHW delivering the digital literacy control receives separate training and attends separate supervision meetings to prevent contamination.

CHWs then support adolescents and caregivers integrating these skills into daily routines, with an emphasis on modeling and reinforcing co-regulation strategies within the home. The intervention concludes with individualized goal setting and maintenance planning to promote sustained resilience. Approximately six months after completion of the core intervention, families are invited to participate in a booster session to reinforce key concepts, re-engage in HRV-BF practice, and reflect on progress. The booster includes a brief review of emotion regulation skills, breathing and HRV-BF techniques, and a discussion of how GRIT strategies have been applied in daily life to support continued practice and maintenance of self- and co-regulation gains.

### Comparison Group: Digital Literacy

The Digital Literacy Program (DLP) serves as an active comparison group in this study. The program is based on lesson content sourced from Common Sense Media’s Digital Citizenship curriculum (Common Sense Education, n.d.). The curriculum offers a structured, interactive, grade-specific curriculum guide to help youth ages 11 to 14, and their caregivers build essential skills for navigating today’s digital world. The program focuses on topics such as media balance, media literacy, online safety, and responsible technology use. The DLP matches the intervention group in duration, CHW facilitation, and level of participant interaction. Providing an active control condition centered on digital behaviors and family engagement.

#### Content.

The DLP curriculum covers six key digital literacy topics, including digital habits, online privacy, digital footprint, digital communication, misinformation, media literacy, and safety. Each session includes a behavior change activity, such as screen time reflection and media balance commitments. These activities are included directly in the lesson and completed during the session. The worksheets guide families through discussions, goal-setting exercises, and practical applications of the core lesson.

### Discontinuation Criteria

Study participants may discontinue participation at any point during the study. The intervention may be discontinued for a participant if safety concerns arise that limits the participant’s ability to continue participation such as psychological distress (e.g. imminent risk of harming self or others), or withdrawal of consent or assent. Unless participants request complete withdrawal, data collected prior to discontinuation will be used for data analysis in accordance with IRB policy.

### Outcomes

The primary outcome is adolescent initiation of regular alcohol and cannabis use. Alcohol and cannabis use will be measured using items from the CDC Youth Risk Behavior Survey (YRBS) and the frequency of use will be assessed using the Timeline Followback (TLFB) method. Regular alcohol or cannabis use is defined as at least weekly use. Secondary outcomes include anthropometrics, heart rate variability, emotional regulation, psychological health, health behaviors, and family functioning. Outcomes will be measured at baseline, post-intervention (2 months), 6 months post-intervention, and 12 months post-intervention.

### Measures

Over the duration of the study, participating youth and caregivers are invited to complete data collection assessments at four timepoints: pre-intervention (baseline), post-intervention (2 months post-baseline), 6-months post-intervention (8 months post-baseline) & 12-month post-intervention (14 months post baseline). Assessments consist of a set of self-report questionnaires and objective measures of heart rate variability (HRV). All questionnaires are completed online through REDCap, a secure database platform. Themes covered in questionnaires include youth and caregivers’ individual substance use and health behaviors, family functioning, and psychological and emotional health. All self-report measures have demonstrated good reliability, including internal consistency and moderate to good test-retest reliability, in previous research with adolescents and adults (36–44). HRV measures are collected directly from the youth and caregiver by the assessment team at three time points: pre-intervention, post-intervention, and 12-month post-intervention.

### Anthropometrics

Anthropometric measures collected from youth and caregiver include height, weight, waist circumference, pulse, and blood pressure.

### Heart Rate Variability (HRV)

HRV is an index of objective physiological measures of stress (18). It is collected using a heart rhythm monitoring system called emWave Pro Plus. The system was developed by the HeartMath Institute, a leader in developing HRV biofeedback technology (45). The software collects real-time HRV data from a non-invasive earlobe clip that is sensitive to heart rate and allows data input to be tracked on a computer. The device is used to capture participants’ HRV in 3 different states: resting (3 minutes), stress prep (3 minutes), and deep breathing (1minute). Changes within an individual’s HRV over time are examined, with higher HRVs reflecting an individual’s ability to quickly return to homeostasis and a more regulated nervous system (46)

### Substance Use

Alcohol, cannabis, and other substances’ use are collected from youth using select multiple-choice items from the CDC Youth Risk Behavior Survey (YBRS) questionnaire that ask about substance use history, frequency, and age of onset. Positive reporting of alcohol or cannabis use by youth prompts a Timeline Followback Method Assessment (TLFB) in which youth are asked to recall and report the estimated amount of consumption across the last 30 days from the day of assessment (47,48). Caregiver’s alcohol and cannabis use is measured using the Alcohol Use Disorders Identification Test (AUDIT-C) and Cannabis Use Disorder Identification Test (CUDIT-R), which assess frequency and amount of substance consumption in the past year (36,40).

### Emotional Regulation

Difficulties in Emotional Regulation- Short Form (DERS-SF) is used to collect data on emotional regulation abilities for both youth and caregivers. The DERS-SF is an 18-item self-report, an abbreviated version of the original 36-item questionnaire (49). Emotional regulation is measured on 6 subscales: strategies, non-acceptance, impulse, goals, awareness, and clarity. Total scores range from 18 to 90, with higher total scores on the DERS-SF indicating greater difficulties in emotion regulation.

### Psychological Health

Psychological flexibility was measured for youth participants using the Acceptance and Fusion Questionnaire (AFQ_Y8)(39). The Acceptance and Action Questionnaire (AAQ-II) was used to measure psychological flexibility in adults. Higher total scores on the AFQ_Y8 and AAQ-II are indicative of lower psychological flexibility.

We measured levels of perceived stress for youth and caregivers using the Perceived Stress Scale (PSS-10). The 10-item questionnaire evaluates stress according to two subscales: perceived helplessness and lack of self-efficacy. A higher overall score is indicative of higher levels of perceived stress.

### Health Behaviors

Nutrition and physical activity amongst youth participants were collected using select multiple-choice items from the CDC Youth Risk Behavior Survey (YBRS) questionnaire. Items asked about the frequency of engagement in physical activity and nutrition, such as the inclusion of food items in the diet (i.e., fruit, green salad, and other vegetables). The Pittsburgh Sleep Quality Index (PSQI) was used to collect data on youth and caregiver sleep behaviors. The PSQI is a 19-item self-report questionnaire that assesses seven component scores: subjective sleep quality, sleep latency, sleep duration, habitual sleep efficiency, sleep disturbances, use of sleep medication, and daytime dysfunction (50). PSQI global scores range from 0 to 21, with higher scores than 5 indicating sleep disturbance.

### Family Functioning

The Family Assessment Device was used to examine family functioning reported by youth and caregivers. The 60-item self-report questionnaire collects data on families’ ability to problem solve, communicate, have distinguished roles, control behavior, and affective response and involvement. Higher overall scores indicate worse levels of family function (42)

### Data Management

A data safety monitoring board will be appointed for this study by month 4. Our board will be composed of five members: three external members with experience working with the population and two senior investigators from our institution who conduct behavioral research with similar populations. They will meet a minimum of two times per year and maintain and approve minutes of meeting. The NIH PO will be kept informed regarding changes to the membership of the DSM board. Data will be reviewed as every 30 participants enters the study. We will conduct interim analysis of safety endpoints to identify possible changes in protocol needed to improve safety. Given the nature of this intervention, traditional medical and clinical trial stoppage rules are not appropriate. Therefore, the DSMB and the PI will make determinations as to whether the trial should be halted in the unlikely event of serious adverse events.

All study data are managed using the secure, HIPAA-compliant Research Electronic Data Capture (REDCap) system hosted by the University of California, Irvine (51,52,52). Screening, randomization, intervention monitoring, and follow-up assessments are maintained in REDCap projects to streamline workflow and maintain participant confidentiality. Access to the project is role-restricted, and all user activity is automatically audited. Youth and caregivers complete their questionnaires independently through individualized REDCap survey links, and branching logic ensures they only view items relevant to their age and role. HRV recordings and anthropometric data are collected by trained assessment staff and entered directly into standardized electronic case report forms with embedded range checks, logic constraints, and mandatory fields to minimize entry errors.

Data quality is maintained through multiple layers of verification. Weekly automated reports flag missing values, inconsistent responses, or out-of-range entries, which are subsequently reviewed and resolved by the Data Manager through a structured query process. In addition, semi-annual data audits verify approximately ten percent of all records against source documents, including fidelity logs, HRV raw files, and attendance records, to ensure accuracy and completeness. All participant data are stored under a unique study identification number. All data will be retained for at least seven years after study completion in accordance with institutional and federal requirements. Only de-identified, analysis-ready datasets will be exported for statistical analyses.

### Data Analysis Plan

Baseline characteristics will be summarized using descriptive statistics to assess group balance. Primary analyses will follow the intention-to-treat principle, with all randomized participants included. Changes in adolescent alcohol and cannabis use will be compared between study arms using generalized linear mixed models (GLMMs) to account for within-subject correlation over time. Alcohol and cannabis use will be dichotomized as no or occasional use versus regular use (weekly or more) to evaluate the intervention’s effect on preventing initiation of regular substance use. Statistical significance will be assessed using two-sided tests with an alpha level of 0.05.

Multilevel mediation analyses will be conducted to examine mechanisms underlying intervention effects, with youth and caregiver emotional regulation specified as primary mediators. Additional exploratory mediators will include heart rate variability, psychological and cognitive flexibility, youth health behaviors (HRV biofeedback practice, sleep, nutrition, physical activity), and environmental factors (parental monitoring, family functioning, and caregiver substance use). Indirect and direct effects will be estimated using residual-based bootstrap methods to generate 95% confidence intervals. Sex differences will be evaluated in secondary analyses by including a sex-by-intervention interaction term.

Our primary analysis will be performed using mixed effects analysis, which provides unbiased estimates when missing data is missing at random (MAR). We will also consider multiple imputations to handle missingness using the Rubin method implemented in R package mice (53,54).

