## Methods

### Study Design and Study Aims

The THRIVE Study is a two-armed RCT designed to evaluate the effects of GRIT, a psychoeducational health coaching intervention aimed at preventing the early initiation of regular alcohol and cannabis use in adversity-impacted adolescents ages 11 to 14 who are at high risk for toxic stress. This study will include two groups: an intervention group receiving the GRIT intervention and an active control group receiving a digital literacy curriculum. The study will assess the impact of the GRIT intervention on self-regulation and substance use outcomes through repeated measures at pre-intervention, post-intervention (2 months post-baseline), 6-month follow-up (8 months post-baseline), and 12-month follow-up (14 months post-baseline).

There are two specific aims for this study: (1) test the efficacy of GRIT on preventing the early initiation of regular alcohol and cannabis use among adversity-impacted adolescents ages 11–14 years who do not regularly use these substances at baseline; and (2) test the mediating effects of youth and caregiver self-regulation on the relationship between the GRIT program and adolescent substance use outcomes. A digital literacy active control group will allow for comparison in youth and caregiver outcomes. We hypothesize that adolescents who receive GRIT will have lower rates of regular alcohol and cannabis use compared to those in the active control group post-intervention, and that youth and caregiver self-regulation will mediate the relationship between the GRIT intervention and youth outcomes.

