
### Sampling

Two hundred and ten adolescent-caregiver dyads (N=420), with adversity-impacted youth aged 11–14, will be recruited. Adolescents are considered adversity-impacted if they score in the high-risk category (4 or more ACEs or any number of ACEs and an ACE-related condition [e.g., school difficulties, symptoms of anxiety and/or depression]). Youth will be recruited from schools, health clinics, and youth-serving community organizations in Southern California. Eligible participants will be randomly assigned to either the GRIT intervention or the active control intervention (i.e., Digital Literacy).

Inclusion criteria for youth include: 1) being aged 11–14 years and scoring in the high-risk category on the ACEs and Toxic Stress Risk Assessment Algorithm; 2) having access to a smartphone and willingness to download an app if randomized to the GRIT intervention; and 3) have a positive, supportive adult such as a parent/guardian/primary caregiver aged 18 years or older who is English or Spanish-speaking and willing to participate in the intervention. The inclusion criteria for caregivers require them to be willing to engage in the intervention alongside the youth participant.

Exclusion criteria for youth participants include: 1) reporting alcohol or cannabis use within the last 14 days; 2) currently being enrolled in another family-based intervention (e.g., family therapy); 3) being in acute distress and requiring immediate care (e.g., imminent risk of harm to self or others, active psychosis); 4) requiring supervised visits by the Department of Children and Family Services (DCFS) with the identified caregiver; and 5) cases where the parent/guardian/primary caregiver declines participation, in which case the family will referred to other community-based programs.

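### The primary outcome is a first event that eligibility sets to essentially zero at baseline, yet the planned GLMM compares changes in visit-by-visit status

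*Protocol article*

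**What the plan says.** All references are to the protocol article.

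- **Outcomes:** "The primary outcome is adolescent initiation of regular alcohol and cannabis use", and "Regular alcohol or cannabis use is defined as at least weekly use". Assessments are at baseline and at 2, 8 and 14 months after baseline.
- **Sampling:** youth are excluded for "reporting alcohol or cannabis use within the last 14 days".
- **Study Design and Study Aims:** Aim 1 concerns adolescents "who do not regularly use these substances at baseline". The hypothesis is worded as lower rates of regular use after the intervention.
- **Data Analysis Plan:** "Changes in adolescent alcohol and cannabis use will be compared between study arms using generalized linear mixed models (GLMMs". The response is binary: "Alcohol and cannabis use will be dichotomized as no or occasional use versus regular use (weekly or more". The stated purpose is "to evaluate the intervention’s effect on preventing initiation of regular substance use".
- **Power and Sample Size:** the effect is framed in the same way, as a 40% smaller change over time in the GRIT arm. The assumed control rates are for initiation: 20% for alcohol and 8% for cannabis.
- **Substance Use:** a positive report triggers a Timeline Followback (TLFB) covering the "estimated amount of consumption across the last 30 days from the day of assessment".

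The article does not say whether baseline is a response in the GLMM, how time is coded, or whether a youth who has once been regular stays counted as an initiator.

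**The concern.** Two stated elements do not fit together.

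First, someone who uses at least weekly has used within the last 14 days. The exclusion therefore sets the primary indicator to 0 at screening for every eligible youth who reports truthfully, in both arms. A between-arm comparison of change from that value adds nothing to a comparison at follow-up. In one natural parametrisation it is also undefined on the logit scale.

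Second, initiation is a first occurrence. A GLMM of status at each visit describes who is a regular user at that visit. A youth who starts and then stops is an event followed by a non-event, and a persistent user is an event at every later visit.

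At stake is what the primary efficacy result means. The present wording admits several models that answer different questions, and the choice among them should not be left until outcomes are known.

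**Working it through.** **No plan figure to reproduce.** The article gives no number for this contrast. Its 105 dyads per arm depends on power-software covariance inputs that it does not print, and nothing below rests on that figure.

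**1. Baseline value.** Weekly use implies use within 14 days, and use within 14 days is an exclusion. Hence the indicator is 0 at screening. Rare exceptions remain possible: use between screening and baseline, or several use days in days 15 to 30 of the TLFB window.

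**2. Change from an all-zero baseline.** With categorical visits, the arm-by-visit coefficient at visit v is

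[logit p(GRIT, v) − logit p(GRIT, 0)] − [logit p(control, v) − logit p(control, 0)].

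Both baseline terms are logit(0) = −∞, so the expression is undefined. This is algebra and does not depend on a dataset.

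**3. Illustration.** One trial was simulated with 105 per arm. Assumptions: control onset of 5%, 12% and 20% by months 2, 8 and 14; rates 40% lower in GRIT; a 30% chance that a regular user is not regular at a given visit. The protocol's 20% is treated as the 14-month rate of first regular use; the interim rates and the reversion rate are not in the documents.

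| Regular users | Baseline | Month 2 | Month 8 | Month 14 | Ever |
|---|---|---|---|---|---|
| Control | 0 | 4 | 7 | 14 | 17 |
| GRIT | 0 | 4 | 5 | 7 | 11 |

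- *Baseline kept, categorical visit by arm (plain logistic fit):* the interaction standard errors were 27, about 49,000 and about 9 million at 10, 25 and 50 iterations. The random-intercept version drifted too (intercept about −41, arm about +18).
- *Where the information lies:* the month-14 interaction printed at 10 and 25 iterations, −0.77, is just the follow-up log odds ratio, ln(7/98) − ln(14/91) = −2.64 + 1.87 = −0.77. Its own standard error is √(1/7 + 1/98 + 1/14 + 1/91) = 0.49.
- *Follow-up only, arm by visit:* the maximised log-likelihood is −125.592, identical to the random-intercept fit with baseline rows. Those rows carry no information.
- *Follow-up only, common arm effect:* random-intercept log odds ratio −0.87 (SE 0.75), so exp(−0.87) = 0.42. The population-averaged GEE gave −0.595 (SE 0.426), so exp(−0.595) = 0.55.
- *Baseline kept, linear time:* arm-by-time −1.54 (SE 1.19) per 14 months. It can be fitted, but the zeros at baseline help to set the slope.

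**4. Status against initiation.** The month-14 ratio is 7/14 = 0.50; the ever-regular ratio is 11/17 = 0.65. Under the assumptions of step 3, with reversion independent between visits, the expected values are:

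- Month-14 status: control 20% × 0.7 = 14.0%; GRIT 12% × 0.7 = 8.4%; ratio 0.60, difference 5.6 points.
- Ever seen regular: control 5% × (1 − 0.3³) + 7% × (1 − 0.3²) + 8% × 0.7 = 4.9 + 6.4 + 5.6 = 16.8%; GRIT 0.6 × 16.8 = 10.1%; ratio 0.60, difference 6.7 points.

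So the gap between 0.50 and 0.65 is sampling variation. The systematic difference in this set-up lies in the absolute risks. In general, if a share r of initiators is not regular at the visit, the status ratio is the initiation ratio times (1 − r in GRIT)/(1 − r in control). The two ratios agree only when reversion is equal in the arms, and an intervention that teaches self-regulation could plausibly change stopping as well as starting.

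**5. Initiation coded as permanent.** If a youth once regular stays coded 1, the only complete follow-up patterns are 000, 001, 011 and 111. A random-intercept logistic model fits such ordered patterns ever better as its standard deviation grows. In 25 simulated trials (84 per arm, permanent onset) the log of that standard deviation exceeded 3 in 25 of 25 with baseline rows removed. With 30% reversion it did so in 0 of 25, both for follow-up only and for baseline kept with linear time.

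**The case against.** The strongest reply is that the article does not state the model that breaks. It names a GLMM on the dichotomy. It does not say that baseline is a response row, that visits are categorical, or that the test is an arm-by-visit coefficient, and such detail commonly sits in an analysis plan that is not shown here. The enormous standard errors are an artefact of using an all-zero reference cell, and the identical log-likelihoods show that follow-up contrasts lose nothing. In a cohort that starts at zero, any later regular use is an initiation. A status model also speaks directly to the hypothesis about rates of regular use after the intervention, and repeated counting of persistent users is ordinary repeated measurement.

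Much of this stands. A reader might infer that the primary model cannot be fitted or is bound not to converge. The documents do not support that, because linear-time and follow-up-only versions behave normally when use can revert. A reader might also blame the eligibility rule for a runaway random-intercept variance. That comes from permanent-event coding and appears without any baseline rows. Nor is the indicator strictly zero for every youth, and it is too strong to say that status at follow-up tells nothing about initiation.

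What the reply does not remove is a mismatch in the article's own text. It commits to comparing changes in an indicator that its eligibility rule holds at essentially zero, and it names a first event as primary while describing a model of current status.

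**Conclusion.** The point holds in limited form.

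- The near-constant baseline follows from the exclusion and the weekly definition, assuming truthful reporting and few new weekly users between screening and baseline.
- Non-estimability is conditional on baseline as a response with categorical visit-by-arm terms.
- The mismatch between initiation and current status holds however time is coded. The GLMM either estimates prevalence of regular use (status coding) or becomes near-degenerate (permanent coding).
- Its numerical size is unknown, because the documents give no reversion rate. The 0.50 and 0.65 show only that the two summaries can diverge in one trial of this size; they are not a forecast of bias.

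It concerns the sole primary efficacy analysis, so it should be settled before outcome data are examined.

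**What to change.** Replace the wording in Data Analysis Plan, and align Outcomes and Power and Sample Size with it:

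1. Baseline is not a modelled response.
2. For each substance, initiation is the first regular use by 14 months among randomised youth not regular at baseline.
3. The primary contrast is the difference between arms in cumulative risk by 14 months, for example from a discrete-time model for first regular use over the 2, 8 and 14-month visits, adjusted for the stratification factors (ethnicity and ACEs score).
4. Small-sample penalisation is an option. With 105 × 0.8 = 84 completers per arm, the protocol's rates and a 40% reduction give about 16.8 versus 10.1 alcohol events and 6.7 versus 4.0 cannabis events.
5. A post-baseline GLMM of current regular use is supportive.

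**Cost.** Wording only, on data already planned. Three downsides should be stated. The rare youth who are regular at baseline leave the at-risk set, so their number should be reported by arm beside the all-randomised commitment. Use between the 30-day TLFB windows may still be missed. The power statement must be redone for this contrast: a simple two-proportion comparison at two-sided 0.025 with 84 per arm has about 20% power for alcohol (20% versus 12%) and 8% for cannabis (8% versus 4.8%). Those values follow from the protocol's own rates and are a separate sample-size matter, but they should be visible when the contrast is fixed.
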